#### Secondary outcomes

5.7.2

Health status will be assessed using the Short Form 36 (SF-36), which measures physical and mental health status across eight domains: physical functioning, role limitations due to physical health, bodily pain, general health perceptions, vitality, social functioning, role limitations due to emotional problems, and mental health. Scores are scaled from to 0–100, with higher scores indicating a better health status for each domain.Quality of life: This variable will be assessed using the Latin American-Spanish adaptation of the World Health Organization Quality of Life-100 (WHOQOL-100). The questionnaire consisted of 100 items that assessed an individual's perception of their quality of life across six domains: physical health, psychological health, social relationships, environment, spirituality, and personal beliefs. Scores are scaled from to 1–5, with higher scores indicating better quality of life.Food security status: This variable will be assessed using the Household Food Insecurity Access Scale (HFIAS), which includes nine questions related to food insecurity over the past 30 days. Responses will be scored on a scale of 0–3, with higher scores indicating greater food insecurity. The total score will be used to determine the level of food insecurity experienced by households.Household dietary diversity: This variable is assessed using the Household Food Insecurity Access Scale (HFIAS), which includes three questions related to the variety of foods consumed by the household. Responses will be scored on a scale of 0–3, with higher scores indicating greater dietary diversity. The total score will be used to determine the household dietary diversity.

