### Questionnaires

5.4

The following validated questionnaires, widely used in Spanish-speaking populations, will be administered to gather comprehensive data from the participants, assessing various aspects of their demographic background, health, socioeconomic status, food security, and quality of life:
General Demographic Questionnaire: This questionnaire will gather basic information about the participants, such as age, education, and employment status.SF-36: This is a widely used self-reported measure of health status that assesses eight domains of health-related quality of life: physical functioning, role limitations due to physical health, bodily pain, general health perceptions, vitality, social functioning, role limitations due to emotional problems, and mental health (43).Survey of Socioeconomic Level Stratification: A questionnaire will be employed to know about the socioeconomic status of the participants based on factors such as income, education, and occupation (44).HFIAS (The Household Food Insecurity Access Scale): This is tool used to assess household food insecurity (45). It will provide insight into the participants' access to nutritious and adequate food.Latin American-Spanish adaptation of the WHOQOL-100 (World Health Organization Quality of Life Questionnaire: This is a self-reported questionnaire that assesses an individual's subjective perception of their quality of life across four domains: physical, psychological, social, and environmental (46).Each of the validated questionnaires that will be used in this study is available in detail through their respective references provided in the manuscript. These references include comprehensive information on the structure, application, and validation of each tool.

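### Household dietary diversity is taken from the food-insecurity scale with the opposite scoring direction, no named items and no reversal rule; the WHOQOL-100 domain count also differs between sections

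*Protocol article*

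**What the plan says.** Section 5.7.2 of the protocol article defines two secondary outcomes from the Household Food Insecurity Access Scale (HFIAS).

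- Food security: the scale is one "which includes nine questions related to food insecurity over the past 30 days". Each answer counts 0 to 3 points, "with higher scores indicating greater food insecurity".
- Household dietary diversity: this also comes from the HFIAS, by way of three questions on how varied the household's food is. Each answer again counts 0 to 3 points, but here "with higher scores indicating greater dietary diversity".

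In each entry the total score is the quantity to be used. Section 5.7 says that outcomes come from the questionnaires already mentioned. Section 5.4 lists these, and presents the HFIAS only as a measure of household food insecurity. Section 4.2 names food security and household dietary diversity as separate items in a secondary objective.

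The WHOQOL-100 is described twice. Section 5.4 says it covers "quality of life across four domains: physical, psychological, social, and environmental". Section 5.7.2 says it covers "quality of life across six domains: physical health, psychological health, social relationships, environment, spirituality, and personal beliefs".

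**The concern.** A single instrument with a single response scale is given two opposite directions in adjacent entries, and nothing connects them. An analyst working from this text cannot tell which three questions make up the diversity score, whether they are part of the nine, or whether the responses are to be turned round before summing.

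Two things are at stake. The first is the sign: if items coded towards insecurity were summed as they are and then labelled diversity, a benefit would appear as harm. The second is distinctness: if the items are shared with the food-security score, a result on diversity adds little to a result on food security, although the objectives list them side by side.

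This is more than detail that an article leaves to a fuller document. The article itself states instrument, number of questions, range, direction and use of the total, and these do not fit together. Section 6.3 adds that all secondary outcomes are predefined and that the stated methods will be followed strictly, so the wording is meant to bind.

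The WHOQOL-100 mismatch is a separate and simpler problem: the same adaptation of the same instrument cannot have both four and six domains.

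**Working it through.** The plan gives no figure that depends on this scoring, so there is none to reproduce. The check compares the text, then does score-range arithmetic and a sign check under stated assumptions.

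**1. The two entries side by side (section 5.7.2).**

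- Food security: HFIAS, nine questions, 0–3, higher is worse.
- Dietary diversity: HFIAS, three questions, 0–3, higher is better.
- Reversal rule: none. Identity of the three questions: not given.

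**2. Could another instrument supply the outcome?** Section 5.4 lists a demographic questionnaire, the SF-36, the socioeconomic stratification survey, the HFIAS and the WHOQOL-100. None is described as measuring variety of diet. That leaves two readings.

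- (a) The three questions are among the nine.
- (b) They are extra questions. The HFIAS would then have 9 + 3 = 12 questions, which the article does not say, and section 5.4 does not mention any on variety.

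**3. Score ranges.** Nine questions: 9 × 3 = 27, so 0–27. Three questions: 3 × 3 = 9, so 0–9. Under reading (a) the shared part is 9/27 = 1/3 of the food-security range.

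**4. Sign of an effect.** Let S be the sum of the three responses.

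- Reading (a), unreversed: a programme that reduces insecurity lowers S. Under the rule that higher means more diversity, this is read as less diversity, which is the wrong sign.
- Reading (a), reversed to 9 − S: the score rises, which is the right sign.
- Reading (b), with questions worded so that higher means more variety: the score rises, which is the right sign.

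A simulation illustrates reading (a). All its settings are assumptions: 200,000 people per group; nine interchangeable items; a shared and an item-specific normal component, each with SD 0.7; cut points at −0.2, 0.6 and 1.2; and a latent improvement of 0.3. The mean differences were:

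- nine-item total: −2.31
- three items unreversed: −0.78
- three items reversed: +0.78

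The size is the same either way; only the sign depends on the missing rule.

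**5. Distinctness under reading (a).** The simulated correlation between the three-item and nine-item totals is +0.89 unreversed and −0.89 reversed. A formula shows how far this depends on the assumed item correlation. For nine items with equal variances and common correlation r, the correlation between a three-item sum and the full sum is

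√[(1 + 8r) / (3(1 + 2r))].

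- r = 0: √(1/3) = 0.58
- r = 0.3: √(3.4/4.8) = 0.84
- r = 0.5: √(5/6) = 0.91

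The overlap alone gives 0.58 even if the items are unrelated, and at moderate item correlations the two scores are close to one measurement.

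**6. WHOQOL-100 domains.** Section 5.4 names physical, psychological, social and environmental: four. Section 5.7.2 names physical health, psychological health, social relationships, environment, spirituality and personal beliefs: six. The difference is 6 − 4 = 2, and it needs no assumption.

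**The case against.** The strongest reply is that the plan, followed to the letter, gives the right sign. It says that a higher score means greater diversity; an analyst who obeys this will reverse the items or use items worded in that direction. The article does not say that the three questions belong to the nine, or that they are summed unreversed, and section 5.4 refers readers to the cited sources for the structure and application of each tool.

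Much of this stands. A reader might infer that the diversity result is certain to come out with the wrong sign, or that a third of the food-security items are demonstrably reused. The document supports neither: both depend on reading (a), and the sign error also needs unreversed summing. A reader might also infer that the plan counts the two outcomes as independent evidence, or that six quality-of-life results will be reported where four were meant. No section sets a rule that combines secondary outcomes, quality of life is described as one variable, and section 6.3 does not commit to one model per domain.

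What the reply does not remove is the gap itself. The literal reading works only if the analyst supplies items or a reversal that the text lacks, and no listed questionnaire is said to measure dietary variety. Nor does it touch the two domain counts.

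**Conclusion.** The point holds as a failure to reconcile, not as a proven sign error. Household dietary diversity has no identified items, a direction opposite to that of its parent instrument, and no dietary-diversity instrument behind it, so it is not validly defined as a separate outcome.

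The size is conditional. If the three questions are among the nine, up to 9 of 27 points are shared. Unreversed, a benefit would be read as reduced diversity; reversed, the outcome mostly repeats food security. If they are separate questions, the sign may be right but the questions are unknown. The simulated ±0.78 and ±0.89 only illustrate the first case and rest on assumed settings.

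The four-versus-six conflict on the WHOQOL-100 is unconditional.

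Severity is moderate. Employment status, income, socioeconomic status, the sample size and the group-by-time estimand for the primary outcomes are unaffected, and section 5.8 calls the study exploratory.

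**What to change.** In section 5.7.2:

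- Identify the three HFIAS questions and say whether they are among the nine.
- Then choose one treatment. Either keep the HFIAS direction (higher is worse) and report them as a food-security sub-score, or state the reverse-coding explicitly, for example 9 minus the sum.
- Do not report household dietary diversity as a separate secondary outcome, here or in section 4.2, unless a separate instrument is named in section 5.4 before baseline. An instrument added later would have no baseline value, and the model in section 6.3 uses baseline as one of its three time points.

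In sections 5.4 and 5.7.2, list the same WHOQOL-100 domains, taken from the scoring source that the article cites.

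The cost is a few sentences, plus either one fewer separate secondary outcome or one more short form for participants to complete at each of the three assessments.

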### Sample size

5.8

The sample size for this study will consist of 80 participants, including 50 in the full intervention group, 20 in the soft skills-only group, and 10 in the control group. This study is exploratory in nature due to resource constraints, particularly funding limitations and logistical challenges in delivering training sessions. The sample size was determined based on the maximum feasible recruitment capacity within the available resources rather than a formal statistical power calculation. While a larger sample would enhance the statistical power of the findings, this study serves as an initial investigation into the effectiveness of the New Dimensions program, providing preliminary evidence that can inform future large-scale studies and programs.

### Recruitment

5.9

The *New Dimensions* program, which is funded by the United States Embassy and Consulate in Ecuador, will be advertised on the social media platforms of the Ecuadorian Development Research Lab (LIDE) and Embassy/Consulate. Furthermore, webinars shared by university authorities will be held to explain the purpose of the program and the steps to apply. We expect that word-of-mouth advertising will help recruit prospective candidates for the program. Prospective students will be directed to the *New Dimensions* website, which includes a button to access an application form in Qualtrics. It is important to note that while the program is financed by the embassy, the research evaluation component of the program is funded by Instituto Tecnológico Argos.

### Assignment of interventions

5.10

The full intervention group, comprising both hard and soft skills training, will be selected from the full pool of applicants based on economic need, academic, and motivational merit by a team of four reviewers. Thus, owing to the nature of this application process, the intervention for the full group will not be randomly assigned. A pool of applicants who narrowly misses being selected for the full intervention group will be created. Participants from the soft skills-only (partial intervention) and control groups will be randomly selected using Microsoft Excel's random-number generator function. Random selection will be conducted within strata defined by city (Quito/Guayaquil), baseline employment status (employed vs. not), and motivation score tertiles to minimize imbalance. Excel RAND() will be used to generate random numbers separately within each stratum, followed by rank-ordering and assignment.

## Data collection, management, analysis and ethics

6

### Data collection methods

6.1

Candidates will submit an online application form in which they have to provide demographic and socioeconomic information as well as their motivation to apply to the program. After submitting this form, the shortlisted candidates will be asked to take a computer-based exam to collect information on their math skills. Applicants will be encouraged to answer all questions. Each candidate who advances to the next stage of the selection process will be interviewed by members of the program's admission committee. All interviewers will record and score their responses. At follow-ups, we will implement the objective employment verification procedures (employer check, optional document upload, LinkedIn observation) for consenting participants.

### Data management

6.2

To ensure the security and confidentiality of the data collected from the study, all information regarding the candidates and their scores will be managed and stored on a secure cloud-based platform. Access to the data will be restricted to the research team and authorized personnel, and appropriate measures will be taken to prevent unauthorized access to or disclosure of sensitive information. Data backups will be created regularly to prevent loss of or damage to the data, and all necessary precautions will be taken to ensure the integrity and reliability of the data throughout the study.

### Statistical plan

6.3

Descriptive statistics will be used to summarize the demographic characteristics of the study population and examine the distribution of outcome variables. Continuous variables will be summarized as means and standard deviations or medians and interquartile ranges depending on their distribution. Categorical variables will be summarized as frequencies and percentages.

To assess the effectiveness of the *New Dimensions program*, we employ a quasi-experimental design with two intervention groups and one control group. The two intervention groups will be compared to the control group to evaluate the impact of the program on employability and well-being outcomes.

To test for differences in baseline characteristics between the intervention and control groups, we used *t*-tests for continuous variables and chi-square tests for categorical variables. To examine changes in the outcome variables over time, we plan to employ linear mixed-effects regression models. Models will include fixed effects for group (full/partial/control), time (baseline/endline/12-month), and the group × time interaction (primary estimand), with random intercepts for participants. These models will allow us to account for the within-subject correlation of repeated measurements over time and adjust for potential confounders, such as age and educational level. We will additionally adjust for city, baseline employment status, and motivation score (tertiles). This will help to control for variations in motivation that could impact outcomes, thereby reducing the risk of false positives. By adjusting for motivation, we aim to ensure that the observed effects are more likely to be attributable to the intervention itself rather than pre-existing differences between groups.

Missing data will be handled using complete case analysis when the proportion of missing data is low and assumed to be missing completely at random (MCAR). For cases where missingness is more substantial, we will implement inverse probability weighting (IPW) to adjust for potential differences between participants who remain in the study and those lost to follow-up. Descriptive comparisons between retained and lost participants will also be performed to assess systematic differences that could influence the results.

All statistical tests will be two-sided, with a significance threshold of *p* < 0.05. Missing data will be addressed using Multiple Imputation by Chained Equations (MICE) under MAR assumptions, with sensitivity analyses including complete-case and IPW approaches. Given the exploratory sample size (*n* = 80), we will emphasize precision of estimates (95% confidence intervals) rather than sole reliance on *p*-values, and will apply small-sample robust standard errors where appropriate. All analyses will be conducted in Stata 19.0.

To prevent undisclosed flexibility in our analysis pipeline, as mentioned before, we have predefined all primary and secondary outcomes and will adhere strictly to the outlined statistical methods. Outcome-neutral conditions are established by employing validated instruments known to avoid floor or ceiling effects. Given that the study is exploratory due to funding and resource constraints, no formal power calculation was performed. Therefore, some analyses, particularly those involving subgroup comparisons (e.g., differences between full and partial intervention groups), should be considered exploratory. Assumptions for our analyses include approximate normality of continuous variables and that data are missing at random (MAR), both of which will be examined through diagnostic and sensitivity checks. Missing data will be addressed using Multiple Imputation by Chained Equations (MICE) under MAR assumptions, and effect sizes with 95% confidence intervals will be reported and compared across imputed and complete-case approaches. Robustness will be evaluated by repeating models both with and without adjustment for baseline motivation scores. Finally, to address potential selection bias from the non-random assignment of participants to the full-intervention group, we will perform propensity-score inverse probability of treatment weighting (IPTW) sensitivity analyses based on age, education, city, baseline employment status, and motivation score.

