### Eligibility criteria and selection process for new dimensions

5.2

Low-income, women-at-risk university students and graduates will be invited through social media, university talks, and other channels to apply for the program. After conducting market research, we found that in the two main Ecuadorian cities, Quito and Guayaquil, the demand for data-intensive roles is greater. As a result, the program will be primarily promoted for women living in either of these two cities.

Participants in the program will be selected after a holistic application process, which will consist of three stages. During the first stage, the candidates have to submit an application form. They will be asked basic personal, academic, and socioeconomic information, as well as two short essay questions in which the applicant have to provide a brief description of their current personal situation and their motivation to apply, respectively. A grader will assign a maximum score of 3 for the “personal situation” short-essay question and a maximum score of 5 for the “motivation” one.

Applications with a “motivation” score of less than or equal to 1 which is considered low will be automatically rejected. Then, all applications with a “motivation” and “personal situation” combined score of less than or equal to 2 (25% out of 8 maximum points) will be rejected as well. All non-rejected applicants at this stage will advance in the application process. The reason behind the decision to reject applicants with low scores is to ensure that only the most motivated candidates are given the opportunity to advance to the next stage.

At the second stage, candidates will be invited to take a computer-based basic mathematical skills exam. Applicants who attend the mathematical skills test will also be invited to the final stage of the process, a 15 min interview. A group of four interviewers will ask applicants six broad questions regarding their socioeconomic status, time management skills, knowledge and interest in data, and the *New Dimensions* program. A rubric will be culturally designed to evaluate all applicants on the clarity of their answers, as well as their motivation.

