#### Primary outcomes

5.7.1

Employment status: Participants will be asked to self-report their current employment status as full-time, part-time, or unemployed.Monthly income: Participants will be asked to report their monthly income in US dollars (Ecuador's national currency).Socioeconomic status: This variable will be assessed using the Survey of Socioeconomic Level Stratification Questionnaire, a validated tool used in Ecuador to measure the socioeconomic status of households (44). Participants will be asked a series of questions related to their household assets, income, and education level.

Objective verification (when consented): At endline and 12-month follow-up we will seek employer confirmation (short phone/email check), accept documentary evidence (e.g., contract or pay-stub upload), and record LinkedIn employment updates. Objective indicators will be used to triangulate self-reports.

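### Three-category employment status is given a linear mixed model with no scoring, and baseline employment is both a response row and a covariate in that model

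*Protocol article*

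**What the plan says.** Section 5.7.1 (Primary outcomes) of the protocol article lists employment status, monthly income and socioeconomic status, without ranking them. On the first it says: "Participants will be asked to self-report their current employment status as full-time, part-time, or unemployed". It attaches no numeric values to the categories.

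Section 6.3 (Statistical plan) names one family of outcome models: "To examine changes in the outcome variables over time, we plan to employ linear mixed-effects regression models". The fixed effects are group, "time (baseline/endline/12-month), and the group × time interaction (primary estimand), with random intercepts for participants". Baseline is thus a level of the time factor and supplies a response row.

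The same paragraph extends the covariate list: "We will additionally adjust for city, baseline employment status, and motivation score (tertiles"). It makes no exception for the model in which employment is the outcome. Section 5.10 (Assignment of interventions) shows how that covariate is coded for stratification: "baseline employment status (employed vs. not), and motivation score tertiles to minimize imbalance".

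Section 6.3 also states: "we have predefined all primary and secondary outcomes and will adhere strictly to the outlined statistical methods".

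**The concern.** The first research question and the primary objective both rest on employment. The model assigned to it cannot be fitted until someone chooses numbers for the three categories, and the size of the stated estimand depends on that choice. A choice made after the data are seen is the kind of flexibility that section 6.3 says it wants to prevent.

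The second issue is narrower. In the employment model, the baseline value appears on the left as a response row and on the right, probably collapsed to employed or not, as a covariate. The article justifies the mixed model by its ability to handle within-person correlation, and this overlap distorts exactly that part of the model.

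**Working it through.** The plan gives no effect size, standard deviation or power figure to reproduce. The inputs from the document are three outcome categories, three visits and arms of 50, 20 and 10 (sum 80).

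**1. Dependence on the score.** The change in mean score equals the sum over categories of score × change in proportion.

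| Shift within a group | Scores 0/1/2 (unemployed/part-time/full-time) | Scores 0/1/3 | In work yes/no (0/1/1) |
|---|---|---|---|
| 40% from unemployed to part-time | 0.40 × 1 = +0.4 | 0.40 × 1 = +0.4 | +0.4 |
| 20% from unemployed to full-time | 0.20 × 2 = +0.4 | 0.20 × 3 = +0.6 | +0.2 |

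Under 0/1/2 the two shifts are equal. Under 0/1/3 the second is larger, and under in-work coding the first is twice the second. The document fixes none of these scorings.

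**2. Double use, complete data.** Baseline employment is constant within a participant. With all three visits present, group × time is estimated from within-participant contrasts, so a constant covariate cancels out of it. The simulation agrees. Its assumptions are not in the documents: latent logistic outcome, random-intercept SD 1.5, scores 0/1/2, the same time shift in every arm (so no group × time effect), and 100 data sets per scenario. For full versus control at 12 months:

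| | Without covariate | With covariate |
|---|---|---|
| Mean estimate | 0.022 | 0.022 (largest difference below 1e-13) |
| Mean SE | 0.360 | 0.360 |
| Random-intercept variance | 0.270 | 0.057 |
| Share of fits with variance below 0.01 | 0% | 6% |

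**3. Why the variance shrinks.** Take binary employment with an assumed latent correlation of 0.6 between visits, which gives a binary correlation of about 0.41 and an outcome variance of about 0.25.
- Shared covariance without the covariate: 0.41 × 0.25 ≈ 0.10.
- One slope has to serve all three rows: (1 + 0.41 + 0.41)/3 ≈ 0.607.
- Residual covariance, baseline with follow-up: 0.25 × (1 − 0.607) × (0.41 − 0.607) ≈ −0.02.
- Residual covariance, follow-up with follow-up: 0.25 × (0.41 − 2 × 0.607 × 0.41 + 0.607²) ≈ 0.07.
- Average over the three pairs: (−0.02 − 0.02 + 0.07)/3 ≈ 0.01.

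A separate simulation of binary employment (400 data sets) gave 0.099 without and 0.011 with the covariate. The empirical SD of group × time was 0.183 in both models, and the rejection rate was 0.048 in both.

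**4. Double use, unbalanced follow-up.** Set-up as in step 2, with average missingness of 25% at follow-up: 12.5% if employed at baseline and 37.5% if not (again an assumption).

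| | Without covariate | With covariate |
|---|---|---|
| Mean SE | 0.406 | 0.390 |
| Random-intercept variance | 0.265 | 0.039 |
| Share of fits with variance below 0.01 | 0% | 29% |
| Rejection rate | 0.05 | 0.06 |

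In a single data set the two estimates differed by up to 0.22, roughly half a standard error.

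**The case against.** **A condensed article leaves model details to an analysis plan.** This does not answer the point. Section 6.3 separates continuous from categorical variables for the descriptive summaries and the baseline tests, then names one linear model for all outcomes and promises strict adherence.

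**The double use does not affect the estimand.** This stands for complete data. A reader might infer that the overlap biases the program effect or inflates the type I error. The algebra and both simulations show otherwise. The shift under unbalanced follow-up is also limited to fits on whatever visits are available. Data completed by multiple imputation are balanced, and so are participant-level complete cases. In a check of 15 complete-case data sets, group × time changed by at most 6e-14. The planned small-sample robust standard errors soften the effect of a wrong variance structure.

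**A linear model for a binary outcome is acceptable.** This stands too. It estimates a risk difference and held its size. The fault is the unscored third category, not linearity itself.

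**Stronger readings that the document does not support.**
- Normality is not assumed for employment status: "Assumptions for our analyses include approximate normality of continuous variables and that data are missing at random (MAR".
- Employment is listed first but is not designated the leading primary outcome.
- Students are recruited ("Low-income, women-at-risk university students and graduates will be invited"), so one might infer that those not seeking work will be counted as unemployed. The questionnaire is not shown, and full-time or part-time is not restricted to formal jobs.
- A spike of zero incomes is plausible, but no figure supports it.

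**The study is declared exploratory and stresses confidence intervals.** This lowers the severity. It does not supply a meaning for the coefficient whose interval will be reported.

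**Conclusion.** The point holds and should be fixed. As written, the employment analysis gives a group × time coefficient whose size depends on an undeclared score. Under 0/1/2 scoring, +0.4 is compatible with a 40-point or a 20-point rise in the share in work. This follows from the text and arithmetic alone.

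The double use of baseline employment is the lesser part. It affects only the employment model and leaves group × time unchanged in complete data. It shrinks the random-intercept variance (0.270 to 0.057, or 0.099 to 0.011 for binary employment), and it can shift estimates when follow-up is unbalanced (up to 0.22 in one data set). Those sizes rest on the simulation assumptions stated above. The planned repeat of the models switches only the motivation score on and off, so it would not reveal the problem.

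**What to change.** In section 6.3, give employment status its own sentence:
- Primary form: in work (full-time or part-time) versus not, at each visit. This matches the employed-or-not split already used for stratification.
- Keep group × time as the estimand and report it as a difference in risk differences, with 95% confidence intervals and the small-sample robust standard errors already planned.
- Secondary form: the three-level status in an ordinal mixed or GEE model.
- Omit baseline employment from the covariates of this one model, because the baseline row already carries it. Leave it in the models for the other outcomes.

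A baseline-adjusted analysis of follow-up rows only (ANCOVA) should be at most a sensitivity analysis. When the groups were alike at baseline it reduced the empirical SD from 0.183 to 0.157 (1 − 0.157/0.183 ≈ 14%). However, the full arm is selected on need and merit, not randomised (section 5.10). In a simulation with no effect, where the full arm differed by ±1 on a stable latent logit (an assumption; 4,000 replicates), ANCOVA averaged ±0.12 and change from baseline averaged about 0.00. ANCOVA would also replace the stated estimand, and making 12 months the primary time would conflict with section 4.2, which treats one year as a secondary objective.

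The cost is a few lines of statistical wording, settled before outcome data are seen. Sample size, visits and questionnaires do not change.
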